#### Statistical analysis of secondary study parameters

The proportion of abnormal ovaries found during primary surgery that necessitate resection (based on the opinion of the operating surgeon) will be presented as a number and percentage of the total group of study patients. This specific group of patients will be analyzed separately since the need for resection is established before the intervention (PSO) takes place.

Per- and post-operative complications will be presented as numbers and percentages. The number of patients with any complication and the number of patients with a more severely complicated course (Comprehensive Complication Index > 20) will be compared between groups using chi-square tests or Fisher exact tests, as appropriate. In the case of differences in baseline variables between the groups, the number of patients with complications or with a severely complicated course will also be compared using logistic regression analyses that include these variables.

The occurrence of *metastatic spread* to the ovaries (based on pathology reports) will be presented as a number and percentage. Because this can only be assessed in the intervention group, comparison between the groups cannot be made.

The occurrence of relapse of intra-abdominal tumors and the occurrence of primary ovarian cancer are compared between groups using Kaplan Meier analysis and log-rank tests. In the case of differences in baseline variables between the groups, the occurrence of relapse or of primary ovarian cancer will be compared using logistic regression analyses that include these variables.

Generic and disease-specific, health-related quality of life will be measured using the EORTC QLQ-C30 and QLQ-CR29 questionnaires. These will provide continuous variable data that are compared between groups using the student’s t-test or Mann Whitney U-test, as appropriate. Furthermore, linear mixed models for repeated measures will be used to estimate the effect of PSO on the quality of life over time.

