### Sample size

The primary study outcome is the occurrence of either CRC metastases in the ovaries or primary ovarian cancer within 3 years after resection of the (primary) colorectal tumor. Based on previous studies, we assume the incidence of synchronous and metachronous colorectal metastases in the ovaries will be 2.0% during the follow-up period [15, 17, 21]. The incidence of primary ovarian cancer is expected to be 0.1% in this period [39]. This gives an overall incidence of 2.1% in cases where PSO is not performed (non-PSO group).

Following PSO, colorectal tumors can no longer metastasize to the ovaries, while the incidence of primary ovarian malignancy should presumably be 0% (PSO group). However, a small risk of primary ovarian malignancy still exists after PSO due to the development of ‘ovarian remnant syndrome’ (ORS) [40–42]. This risk is estimated to be approximately 0.01% for the PSO group.

Based on these assumptions and an alfa of 0.05 with power of 80%, a sample size calculation was performed using an online sample size calculator for comparison of two proportions [43]. This gave a sample size of 371 patients per group, or 742 in total.

Since all eligible patients are not randomized, it is necessary to correct for possible confounders. According to the one-in-ten rule, at least 10 events (of ovarian malignancies) are needed per factor studied in order to achieve sufficient statistical power [44]. Besides PSO, correction will also be made for age as another possible confounder.

Based on current clinical practice, we estimate that about half of all postmenopausal CRC patients undergo PSO during resection of their colorectal tumor. Therefore, we expect the two study groups to be approximately equal in size. The estimated incidence of ovarian malignancies in the total study population will thus be 1.055% (average of 2.1% and 0.01%), thus requiring a sample size of at least 1896 patients (20/0.01055).

Finally, after taking into account a dropout rate of 5%, at least 1996 patients should be recruited into the study.

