#### Statistical analysis of the primary study parameters

For each group, the number of patients who are alive and without evidence of disease relapse after 3 years of follow-up will be determined. Kaplan–Meier curves with the end-point of disease-free survival will be constructed and the log-rank test will be used to compare 3-year disease-free survival rates between groups.

In the case of differences in baseline variables between the two groups, Cox regression analyses including these variables will be performed. Univariate analysis will first be used to identify possible confounders. Multivariate Cox regression analysis will then be performed including ‘group’ (PSO or no PSO), with possible confounders as independent variables and disease-free survival as the dependent variable.

The NNT to prevent one case of ovarian cancer will be calculated according to the method of Lubsen et al*.* [35]. NNT describes the number of patients required to undergo PSO in order to gain 1 year of disease-free survival.

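### Adjusted analysis of intra-abdominal relapse and primary ovarian cancer switches from log-rank to logistic regression, and for primary ovarian cancer the plan's own rates give only about one event to model

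*Protocol article*

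**What the plan says.** Under 'Statistical analysis of secondary study parameters', the Protocol article takes intra-abdominal relapse and primary ovarian cancer together. Unadjusted, they "are compared between groups using Kaplan Meier analysis and log-rank tests". If the groups differ at baseline, "the occurrence of relapse or of primary ovarian cancer will be compared using logistic regression analyses that include these variables".

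For disease-free survival, under 'Statistical analysis of the primary study parameters', the same circumstance gets a different tool: "In the case of differences in baseline variables between the two groups, Cox regression analyses including these variables will be performed".

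The 'Sample size' section supplies the rates. Without PSO, "The incidence of primary ovarian cancer is expected to be 0.1% in this period", the period being three years. After PSO a small risk of primary ovarian malignancy remains: "This risk is estimated to be approximately 0.01% for the PSO group". The same section calls correction for confounders necessary because patients are not randomized, adopts a rule of at least 10 events per factor, and arrives at 1896 analysable patients (1996 with 5% dropout) in two groups of roughly equal size.

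On incomplete follow-up, the protocol uses a withdrawn patient's data up to withdrawal ('Participant timeline') and does not replace missing data ('General statistical analysis'). It does not say how deaths are handled for these two endpoints.

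**The concern.** There are two problems, and they should be kept apart.

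**The adjusted method does not match the unadjusted one.** Kaplan-Meier and log-rank use the time of each event and let a patient contribute until she leaves observation. Logistic regression uses neither. A woman who dies or withdraws before 36 months without the event has to be coded as event-free or left out, and the text does not choose. The result is an odds ratio, whereas the log-rank test compares hazards. If the crude and adjusted results differ, a reader cannot tell whether confounding or the change of method is responsible. In a preference cohort the adjusted result is the one that carries weight.

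**One of the two endpoints is too rare for any model.** A multivariable comparison of primary ovarian cancer, or a non-significant log-rank test, would look like evidence about PSO while carrying almost none. The Discussion hopes that the results will inform individual decisions and possibly guidelines, so this matters even for a secondary analysis.

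**Working it through.** **1. The plan's own sample size.** Inputs from 'Sample size': 2.1% without PSO, 0.01% with PSO, alpha 0.05, power 80%. Sidedness is not stated; two-sided is assumed.

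- Unpooled variance: n = (1.96 + 0.8416)² × (0.021×0.979 + 0.0001×0.9999) / (0.021 − 0.0001)² = 7.849 × 0.020659 / 0.00043681 ≈ 371.2, or 372 rounded up. The pooled-variance version gives 374. The protocol states: "This gave a sample size of 371 patients per group, or 742 in total". A one-sided test gives 295 and does not match.
- Average incidence = (2.1% + 0.01%)/2 = 1.055%; 20/0.01055 = 1895.7, so 1896.
- 1896/0.95 = 1995.8, so 1996.

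The plan's figures reproduce, so 1896 (948 per group) is a fair basis for the next step.

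**2. Expected primary ovarian cancers.**

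- Non-PSO: 948 × 0.001 = 0.948
- PSO: 948 × 0.0001 = 0.095
- Total: 1.04 (1.10 if all 1996 are analysed)

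Poisson probabilities with mean 1.0428:

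| Number of events | Probability |
|---|---|
| 0 | 0.352 |
| 0 or 1 | 0.720 |
| 4 or more | 0.022 |
| 10 or more | about 2 × 10⁻⁷ |

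**3. Against the ten-events rule.** The average rate is (0.001 + 0.0001)/2 = 0.00055. One factor needs 10/0.00055 ≈ 18,182 patients; two factors (PSO and age) need 20/0.00055 ≈ 36,364. The chance of no event at all in the PSO group is exp(−0.0948) ≈ 0.91, and then no finite log odds ratio for group can be estimated. A Cox model has the same problem, so changing the regression does not rescue this endpoint.

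**4. What the log-rank test would need.** With equal groups and few events, if all d events fall in one group, chi-square ≈ (d − d/2)²/(d/4) = d.

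- 3 versus 0: chi-square about 3, p about 0.08
- 4 versus 0: chi-square about 4, p about 0.045

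At least four events are therefore needed, and their probability is about 2%.

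**5. Absolute risk of relapse, if it is read from Kaplan-Meier.** The document gives neither a relapse rate nor a mortality rate, so this is illustration only. Assume constant hazards, deaths censored, a 3-year 1−KM relapse risk R of 10% and a competing mortality D. Let a = −ln(1−R) and b = −ln(1−D). The cumulative incidence is a/(a+b) × (1 − exp(−(a+b))).

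Example for D = 20%: a = 0.1054, b = 0.2231, a+b = 0.3285; 0.3207 × 0.280 = 0.0898.

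| Assumed 3-year competing mortality | 1−KM | Cumulative incidence | Relative overstatement |
|---|---|---|---|
| 5% | 10% | 9.75% | 2.5% |
| 10% | 10% | 9.50% | 5.3% |
| 20% | 10% | 8.98% | 11.4% |
| 30% | 10% | 8.44% | 18.5% |

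The relative overstatement hardly depends on R: over R from 0.1% to 15% it stays at roughly 3% to 19% across these mortality values. For primary ovarian cancer at 0.1% the absolute difference is negligible (0.097% down to 0.084%).

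**The case against.** The best defence is that these are secondary analyses with little to lose. Five years of follow-up are planned and 5% dropout is assumed, so loss before 36 months should be small apart from deaths. When an event is rare, the odds ratio and hazard ratio nearly coincide. Primary ovarian cancer alone is not a row of Table 1, and that table lists intra-abdominal relapse simply as a number. All of this stands and limits the size of the problem. It does not explain why the protocol uses Cox for disease-free survival and logistic regression here, and it does not make one expected event enough for a model.

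A reader might also infer more than the document supports:

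- **That the plan censors deaths.** This is the usual default when Kaplan-Meier is applied to an endpoint without death, but it is not written. How deaths are coded may be settled in a fuller document.
- **That the planned tests are biased by competing death.** With deaths censored, the log-rank test remains a valid comparison of cause-specific hazards. The upward bias concerns 1−KM read as an absolute risk, and the section commits only to a comparison between groups.
- **That the 2.1% incidence or the NNT is inflated by this sentence.** Those figures belong to the primary composite of metastatic and primary ovarian malignancy, which this sentence does not cover.
- **That six events, all in one group, are needed for significance.** That is the Fisher threshold (5 versus 0 gives p = 0.062, 6 versus 0 gives p = 0.031). The plan names the log-rank test, for which about four suffice, although that asymptotic approximation is weak with so few events.
- **That adjusted modelling of relapse is infeasible too.** The protocol gives no relapse rate, so this cannot be shown.

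**Conclusion.** The point holds in two parts.

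First, the switch to logistic regression is explicit. It discards event and censoring times, changes the quantity estimated and conflicts with the Cox adjustment for disease-free survival. Its numerical effect on relapse cannot be derived from the document; it depends on how many women die or drop out before 36 months and on whether that differs between groups.

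Second, on the protocol's own rates and 948 patients per group, about one primary ovarian cancer is expected. The prescribed adjusted model fails the protocol's own ten-events rule by a wide margin, and the log-rank test has almost no chance of being informative. This rests on the stated 0.1% and 0.01% rates and on equal group sizes.

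The competing-risk issue is conditional. It matters only if 36-month relapse risks are reported as 1−KM with deaths censored, and the 3–19% relative overstatement rests on assumed mortality of 5–30%.

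**What to change.** In 'Statistical analysis of secondary study parameters':

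1. For intra-abdominal relapse, replace logistic regression by cause-specific Cox regression for the adjusted comparison, in line with the analysis of disease-free survival.
2. For primary ovarian cancer, report the number of events and an exact confidence interval per group. Specify no multivariable model, and draw no inference from a log-rank test.
3. If absolute 36-month relapse risks are reported, estimate them as cumulative incidence with death as a competing event, with 95% confidence intervals, and say so.

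The cost is a change of wording and a little extra analysis. Event and death dates are already needed for disease-free and overall survival, and the sample size does not change.

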### Explanation for the choice of comparators and efficacy of PSO

The primary goal of implementing PSO is to improve the health of individual women by preventing the development of ovarian malignancies (primary or metastatic), thus improving disease-free survival, preventing additional treatment-related morbidity, and ultimately improving overall survival. As such, PSO could potentially be a cost-effective procedure, especially from an oncological point of view [26].

Fear of cancer recurrence is an important issue for CRC survivors [33]. A patients’ ability to choose additional prophylactic surgery could be helpful in reducing their fear, since the risk of subsequent metastatic or primary ovarian cancer is removed. Moreover, this supports the practice of “shared decision making”. Beginning in 2020, counseling for PSO (preference of “yes” or “no” to PSO) started to be implemented in the CRC care pathway in several Dutch hospitals. Consequently, the impact of PSO can be prospectively evaluated.

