### Randomization, blinding and treatment allocation

Because this study will evaluate the effects of PSO that are facilitated by an altered CRC care pathway, randomization and blinding are not applicable. The two different patient groups are formed based on patient preferences.

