### Study procedures

Complications will be scored according to the Clavien-Dindo classification [36, 37]. Furthermore, the Comprehensive Complication Index [38] is a composite score that summarizes the patients’ postoperative wellbeing regarding complications based on the Clavien-Dindo classification. Both scores will be determined after surgery.

Health-related quality of life (HRQL) will be measured using EORTC QLQ-C30 for cancer patients in general, and EORTC QLQ-CR29 specifically for CRC patients. The outcomes will be measured at baseline, at 3 months, and at 1-, 2-, and 3-year(s) after surgery. Differences in outcomes between the two groups will be analyzed statistically.

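### The t-test or Mann-Whitney comparison of quality of life between self-selected groups uses neither the baseline score nor confounders, and the added mixed model is not said to govern

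*Protocol article*

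**What the plan says.** Under Randomization, blinding and treatment allocation, the protocol article states: "The two different patient groups are formed based on patient preferences". Under Sample size it draws the consequence: "Since all eligible patients are not randomized, it is necessary to correct for possible confounders".

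Study procedures schedules the quality-of-life questionnaires: "The outcomes will be measured at baseline, at 3 months, and at 1-, 2-, and 3-year(s) after surgery". Table 1 lists the same five occasions.

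Under Statistical analysis of secondary study parameters, the questionnaire scores are to be "compared between groups using the student’s t-test or Mann Whitney U-test, as appropriate". The next sentence, joined by the word Furthermore, adds that "linear mixed models for repeated measures will be used to estimate the effect of PSO on the quality of life over time". It does not list the model's terms, and nothing says which of the two analyses carries the conclusion.

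Other outcomes have an explicit rule for differences in baseline variables:
- Disease-free survival: Cox regression including those variables (Statistical analysis of the primary study parameters).
- Complications: the numbers of patients "will also be compared using logistic regression analyses that include these variables".
- Relapse and primary ovarian cancer: "the occurrence of relapse or of primary ovarian cancer will be compared using logistic regression analyses that include these variables".

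The quality-of-life paragraph has no such rule.

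**The concern.** A two-sample test on follow-up scores estimates the effect of PSO only if the groups would have scored alike without it. Patients who choose an extra prophylactic operation may differ from those who decline in age, fitness, comorbidity or outlook, and each of these can move a quality-of-life score. The protocol accepts this reasoning in general and acts on it for three other outcomes. For quality of life it fixes a between-group comparison that has no place for the baseline score or for any confounder.

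The effect of PSO on quality of life is a stated secondary objective, and the Discussion treats quality of life and complications as what patients will need in order to weigh the operation. A difference that existed before surgery, reported as benefit or harm of PSO, would enter counselling directly. The sample size is set by a rare cancer outcome, so it is large for a continuous score, and small selection differences would readily reach significance.

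**Working it through.** **1. Where the group size comes from.** The protocol gives no sample size, SD or target difference for quality of life, so the group size is taken from the primary outcome. Its figures reproduce:
- With 2.1% versus 0.01%, two-sided alpha 0.05, power 80% and unpooled variance, n per group = (1.960 + 0.842)² × (0.021 × 0.979 + 0.0001 × 0.9999) / (0.0209)² = 371.2, against the stated 371. The pooled formula gives 374.
- 20 / 0.01055 = 1895.7, so 1896; 1896 / 0.95 = 1995.8, so 1996.
- With about equal groups, 1896 / 2 = 948 evaluable patients per group.

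**2. The simple test under no PSO effect.** Assumption: a stable difference of d SD between the groups, the same at baseline and follow-up. Neither d nor the SD is in the document.
- Standard error of the difference in SD units: √(2/948) = 0.0459.
- Rejection probability: Φ(d/SE − 1.96) + Φ(−d/SE − 1.96).
- d = 0.1: d/SE = 2.18, rejection 58.6%.
- d = 0.2: d/SE = 4.35, rejection 99.2%.

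With fewer completed questionnaires the rates fall but do not return to 5%. At 371 per group, SE = √(2/371) = 0.0734, d/SE is 1.36 and 2.72, and the rates are about 28% and 78%. The bias in the estimate stays at d whatever the group size.

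**3. Three ways to use the data.** Simulation with 2000 replicates, 948 per group, no PSO effect, the same stable difference, and an assumed correlation r between baseline and follow-up of 0.5 or 0.7:

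| d (SD) | r | t-test: rejects / estimate | Change from baseline (group-by-time): rejects / estimate | Baseline as covariate: rejects / estimate |
|---|---|---|---|---|
| 0.1 | 0.5 | 59% / 0.10 | 5% / 0.00 | 23% / 0.05 |
| 0.1 | 0.7 | 58% / 0.10 | 5% / 0.00 | 16% / 0.03 |
| 0.2 | 0.5 | 99% / 0.20 | 5% / 0.00 | 70% / 0.10 |
| 0.2 | 0.7 | 99% / 0.20 | 6% / 0.00 | 45% / 0.06 |

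The last column follows d × (1 − r): for example 0.2 × (1 − 0.5) = 0.10. Baseline as a covariate alone therefore leaves part of a stable selection difference in the result.

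**4. How far this depends on stability.** If the difference instead regresses toward a common mean, the simple test carries over r × d: for d = 0.1, 0.05 to 0.07 SD. The change-from-baseline contrast then errs the other way by (1 − r) × d, 0.03 to 0.05 SD. The simple test is biased in both cases. This is also why confounder adjustment is needed beyond any handling of the baseline score.

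**The case against.** The strongest reply is that the mixed model is the analysis the protocol names for estimating the effect of PSO, and that baseline is one of its five scheduled occasions. A repeated-measures model with a group-by-time term would not count a stable baseline difference as an effect, as the table shows. A reader might infer that the whole quality-of-life analysis turns any baseline difference into a PSO effect. The documents do not support that; the problem lies in the simple comparison.

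A reader might also infer that the mixed model leaves out baseline and confounders. The article does not list the model's terms, and silence is not exclusion. Such detail commonly sits in a full protocol or analysis plan that is not shown, so its brevity is no fault here.

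Nor does the article say that anxious patients choose PSO. The sentence that "additional prophylactic surgery could be helpful in reducing their fear" describes a possible benefit of having the choice. It says nothing about who chooses, or about baseline scores.

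Finally, all baseline parameters are to be compared between groups, so an imbalance could be seen. Table 2 does not list the questionnaire scores, however, and even a visible imbalance has no stated consequence for this outcome.

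What remains is what the text does fix: an unadjusted comparison of self-selected groups, no adjustment rule where three other outcomes have one, and no order between two analyses that could disagree.

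**Conclusion.** The point holds for the t-test or Mann-Whitney comparison and for the missing order between the two quality-of-life analyses. That comparison conflicts with the protocol's own statement that confounders must be corrected for, and it would report a pre-existing difference as an effect of PSO. With 948 per group and no true effect, a stable 0.1 SD difference would be significant about 59% of the time and 0.2 SD about 99%. These figures illustrate the mechanism and do not predict it: the size and stability of the difference are assumed, and 948 supposes complete questionnaires. No documented imbalance lies behind them.

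This is worth correcting before analysis, since quality of life is meant to inform patients' decisions. It is a secondary outcome, and neither the primary result nor the sample size is affected.

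**What to change.** State that the linear mixed model is the quality-of-life analysis. Enter baseline as one of the repeated occasions, with group, visit, group-by-visit, age and the same baseline confounders used for the other outcomes. Let the confounders interact with visit; as main effects alone they adjust the level of the score and hardly touch the difference in change. Baseline as a covariate alone is not enough, for the reason shown in the table.

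Report the adjusted group difference in change from baseline, with 95% confidence interval, at 3, 12, 24 and 36 months. Keep the t-test or Mann-Whitney results as descriptive only.

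The cost is a change of wording and a little more analysis work. The baseline questionnaires and the covariates are already being collected.
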